### Recruitment

A subject will be considered enrolled in the study only after providing written consent. No study-specific data will be collected until then. The recruitment procedures for the sample groups are described below:

For Group A, healthy controls will be recruited via the standard outlets, such as the clinic’s website and social media accounts.For groups B and C, patients’ medical files from the MAC registry of our clinic will be screened for inclusion and exclusion criteria. Based on the known distributions of PROM scores (instrument: Core Outcome Measures Index [COMI] [23]) in the registry at 2 and 5 years, the patients’ scores will be categorized as normal/poor scores.

For groups B1 and C1, lists of patients will be generated and ordered by age and sex. Beginning with each patient nearest to age 35, 38, 41, 44, 47, 50, 53, 56, 59, and 62 years, the following recruitment procedure will occur: if no exclusion reason was found, the patient will be contacted by phone by the study nurse and offered study participation. If the patient refuses or cannot be reached after 3 attempts of contact, the next patient within the same age group will be screened and contacted. This ensures a balanced age distribution within sex within the groups. Lists of patients for groups B2 and C2 (by sex) will be generated and ordered by COMI score (decreasing), and patients will be contacted successively.The poor outcomes group B2 consists of patients with scores ≥2.The normal outcomes group B1 is defined as patients closely around the median COMI scores of their respective group (determined medians are: 2-year, females, 0.9; 2-year, males, 0.7; 5-year, females, 0.5; 5-year, males, 0.5).

For Group D, all patients scheduled for unilateral TKA surgery at the site and fulfilling the inclusion criteria will be informed about the study and asked for participation. Screening is done by the study manager as soon as the operation is booked. If the patient is eligible, the study nurse will inform the patient by phone about the study and ask for participation. If the patient is interested, a brochure with information about the study will be sent in written form to the patient to consider participation carefully at home for at least 24 hours. This will be done successively until the sample size of 10 males and 10 females is reached.

### Study Procedures

The overall study duration is 2 years. Recruitment will last for 6 months. For a patient, the duration of the study is 9 months, with one visit at baseline and one visit at 9 months. All measurements will occur at the clinic, including anthropometric data, clinical examination, and functional and temperature assessments. Additionally, the participants should fill in PROMs, which are provided as an online questionnaire via the Research Electronic Data Capture (REDCap; Vanderbilt University) application. If preferred, a paper version of the questionnaire can be provided to the patient. Participants can do this at home.

### Anthropometric and Patient Data

The following data will be collected from the patient’s medical file: sex, age, height, weight, BMI, body fat percentage, comorbidities, and adverse events since the knee operation.

#### EOS Radiography

Long-leg radiographic images will be acquired in a standing position as stereoradiography using the EOS Edge (EOS X-Ray Imaging Acquisition System). The photon counting detector allows for a dose reduction by a factor between 8 and 10 compared to conventional X-ray radiography [24,25]. EOS imaging of the knee has been validated for osteoarthritis grading using KL grading scores [26].

For all participants, bilateral long-leg, standing EOS images in anteroposterior view will be retrieved and analyzed for:

Osteoarthritis grading (KL grade 0‐4)Compartmental joint space widthLeg alignment angles:Knee joint alignment (normal, varus, and valgus) measured with hip-knee-ankle angleMechanical axis lengthProximal tibia widthMechanical axis deviationJoint anglesMechanical lateral distal femoral angleMechanical medial proximal tibial angle

#### MRI Technique

Both knees of the participants will be scanned using a 3 Tesla MRI scanner (Magnetom Prisma; Siemens) without any contrast agent (Table 2). MRI allows visualization and assessment of structural changes in joint tissues, such as cartilage, meniscus, and subchondral bone. A radiologist will use the MRI Osteoarthritis Knee Score (MOAKS) system to score these degenerative structures in osteoarthritis semiquantitatively. The MOAKS score has demonstrated very good to excellent reliability [27] and grades tissues in 7 different subregions of the knee [28].

**Table 2. T2:** Acquisition parameters of magnetic resonance imaging (MRI) sequences.

MRI^a^ sequence	STIR^b^	T1 TSE^c^	PD^d^ dixon	PD TSE FS^e^
Orientation	coronal	coronal	3D [4,5]	3D [6,7]
Field of view (mm)	154	160	160	160
Repetition time (ms)	4850	558	5010	4200
Echo time (ms)	31	7.1	44	42
Number of slices	28	28	34	31
Slice thickness (mm)	3	3	2.5	2.7
Distance factor (%)	20	15	15	10
Voxel area (mm^3^)	0.6×0.6×3	0.5×0.5×3	0.4×0.4×2.5	0.4×0.4×2.7
Pixel bandwidth (Hz/Px)	260	340	334	260
Flip angles (deg°)	180	180	180	180

a MRI: magnetic resonance imaging.

b STIR: short tau inversion recovery.

c TSE: turbo spin echo.

d PD: proton density.

e FS: fat saturation.

#### AE Test With Inmodi Knee Brace

The tests will be done with the Inmodi knee brace (v2; Figure 1) for AE assessment of both knees simultaneously [18]. The brace is designed to not hinder movement and is made of biocompatible materials (polylactic acid/thermoplastic polyurethane) covered by silicon commonly used in orthopedics for direct skin contact. All the embedded electronics are fully isolated, without possible contact with the patient. The device consists of 2 parts to be attached on the limb with the help of straps (Figure 2):

The main part is to be positioned on the calf. This part has an embedded inertial measurement unit (IMU) module to collect kinematic data on the lower part of the limb and 2 microphones positioned in an enclosure covered by removable silicone. The microphones are placed at each extremity of a flexible arch to be positioned on the medial and lateral subpatellar regions. This mainframe also has a battery, microcontroller, and embedded flash memory to save the raw data.A secondary part to be positioned on the thighs and connected by USB to the main part. This secondary part has an IMU module to collect the kinematics of the upper part of the limb and an interface with buttons to start/stop the recording of all sensors.

**Figure 1. F1:**
[figure not shown]
Upper part (positioned on the thigh) and lower part (positioned on the calf) of the Inmodi knee brace.

**Figure 2. F2:**
[figure not shown]
The Inmodi device from the top (left) and the bottom (right). The green silicone covers can be removed from the microphone frames for cleaning.

All the sensors collect data in a synchronized manner: the microphones (SPH0645LM4H-B; Knowles) have a sampling rate of 22000 Hz, and the IMU (BNO080; CEVA Hillcrest Labs) has a frequency of 100 Hz. The microphones were chosen to have a sampling rate covering the relevant acoustic information suggested in the literature [9,11,15]. We decided to use airborne microphones to improve the device’s usability for easy positioning without needing extra tapes to maintain contact sensors on the skin and potential associated rubbing artifacts from them. The literature has reported that, despite having a lower signal-to-noise ratio, airborne AEs can be collected by Micro-electro-mechanical systems microphones as an alternative to contact sensors to assess knee health [15]. The advantage of using air microphones over contact microphones resides in the clinical applicability of the solution, which requires minimal preparation from the medical workers. However, such an approach requires a design to ensure a consistent distance between the airborne microphone and the skin to keep the microphone’s sensitivity to collect knee sounds. The Inmodi device was designed to keep the microphone at a distance of 6.5 mm from the skin while preventing any skin contact with the microphone membrane, thanks to a rigid frame encapsulating the microphone covered by a silicone piece. The silicone piece is the only part in contact with the skin, providing a damping of artifact noise due to possible friction, and it is removable for cleaning between patients.

The tests are based on recommendations by the Osteoarthritis Research Society International (OARSI) for people with knee osteoarthritis [29]:

Unloaded flexion-extension (F-E) of the knee in a seated position, starting with a knee angle of 90°, followed by a full extension and returning to the starting position (6 times). A video will guide the pace of the motion to normalize the velocity among patients (comfortable speed).Sit-to-stand test (STS) at a comfortable pace (6 times). Force plates (FP-BTA; Vernier) will be used during this exercise to assess the ground reaction force for each sole and detect any asymmetrical loading of the joints.One-step test (OST) is an exercise step platform, which will be used to perform a complete ascent and descent at a comfortable speed (6 times per leg).Walk test at a comfortable pace (10m ×2 times).

The following measurements will be performed together with the AE tests:

Temperature assessment: thermal distribution of the knee joint will be assessed with a far infrared thermal sensor array (MLX90640; Melexis) to evaluate the state of inflammation. Localized thermal images will be recorded at three time points: (1) at the beginning of the whole test, just after arriving, (2) after warming up (5 minutes on a stationary bicycle), and (3) at the end of all tests.Pain assessment: after the test session, the level of knee pain will be assessed using a visual analog scale. Participants will quantify the maximum knee pain experienced during the tests for each knee separately by placing a vertical mark on a 10 cm horizontal line. The line ranges from 0 (“no pain at all”) to 10 (“not endurable pain”).

#### PROMs

The following PROMs questionnaires were sent out by email or paper form depending on participants’ preference and were completed in their homes.

Oxford Knee Score (OKS): this instrument contains 12 questions about an individual’s activities of daily living and how they have been affected by pain over the last 4 weeks. Its summed score ranges from 0 (severe functional problems) to 48 (excellent knee function) [30,31].Core Outcome Measures Index (COMI) knee: assesses the main outcomes of importance to patients with knee problems (pain, function, symptom-specific well-being, quality of life, disability). It is a 6-item multidimensional instrument with 5 domain scores for pain (item 1), function (item 2), symptom-specific well-being (item 3), general quality of life (item 4), and disability (average of items 5 and 6) are averaged to give a COMI score ranging from 0 to 10 (the higher the score, the worse the status) [32].University of California at Los Angeles (UCLA): an activity rating scale, which rates the activity level of joint replacement patients globally from 1 to 10. The patient indicates her/his most appropriate activity level (level 1 = “no physical activity, dependent on others”; level 10 = “regular participation in impact sports”) [33].Knee Injury and Osteoarthritis Outcome Score (KOOS): an instrument to assess the patient’s opinion about their knee and associated problems. There are 5 subscales with individual sum scores normalized to 0-100 (0 = “extreme symptoms”; 100 = “no symptoms”): pain, other symptoms, function in daily living, function in sport and recreation, and knee-related quality of life. A total score of all subscales combined has not been validated [34].Forgotten Joint Score 12 (FJS-12) is a concise 12-item PROM that evaluates patients’ ability to forget their joints daily. Each item is answered within a 5-point Likert scale with the following response options: never (0); almost never (1); seldom (2); sometimes (3); and mostly (4) [35].

### Signal Segmentation and Denoising

This involves the isolation of the different movement phases of the acoustic signals, the removal of frequency components of low interest, and the separation of the acoustic signal into different sources (sounds from the knee, ambient sounds, sounds from the device, etc). The segmentation will be based mostly on the kinematic data, using the relative angles between the upper and lower parts of the device to set the beginning and end time of each repetitive movement. For denoising, most previous literature suggests relevant acoustic information is below 20kHz, and typically a bandpass filtering from 100 Hz up to 10‐16,ooo Hz is applied depending on the study [9,11,15]. We will start from this approach, relying on standard digital filters such as Butterworth filters and complementary transforms such as wavelets. Different cutoff frequencies (3, 6, 8, 10, and 16,000 Hz) will be explored to minimize the amount of data to process and simplify feature extraction. Data separation will be achieved through techniques such as empirical mode decomposition and independent component analysis. To reinforce this separation, a further clustering analysis will be performed with techniques such as Density-based spatial clustering of applications with noise to try to unveil robust causal relations between audio segments and sources.

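### At the stated 22,000 Hz sampling rate the planned 16 kHz filter cutoff cannot be implemented, and the claim of covering the literature's acoustic band fails above 11 kHz

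*Protocol article*

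**What the plan says.** Two sections of the Protocol article bear on this.

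AE Test With Inmodi Knee Brace (the text below Figure 2) gives the recording rate: "the microphones (SPH0645LM4H-B; Knowles) have a sampling rate of 22000 Hz". It then justifies it, citing references 9, 11 and 15: "The microphones were chosen to have a sampling rate covering the relevant acoustic information suggested in the literature".

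Signal Segmentation and Denoising, citing the same three references, states that "most previous literature suggests relevant acoustic information is below 20kHz". It reports that "typically a bandpass filtering from 100 Hz up to" an upper edge of 10 to 16 kHz is applied, depending on the study. The plan follows suit: "We will start from this approach, relying on standard digital filters such as Butterworth filters", together with wavelets. It then sets out the grid: "Different cutoff frequencies (3, 6, 8, 10, and 16,000 Hz) will be explored to minimize the amount of data to process". The stated aims of the grid are to reduce the data volume and simplify feature extraction.

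The article mentions no second audio channel, no other sampling rate and no upsampling.

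**The concern.** A recording sampled at rate fs holds information only up to fs/2. The stated rate and the highest planned cutoff therefore cannot both stand, and neither can the stated rate and an unqualified claim to cover the band used in the cited studies.

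Three things are at stake:

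- **Reproducibility.** The Statistics section promises open access to the exact feature sets and analysis code. Code that follows the filtering section would stop with an error at 16 kHz, or the setting would have to be dropped or changed without explanation.
- **Interpretation.** The objective is to identify acoustic biomarkers. A reader who takes the coverage sentence at face value would believe that the full literature band had been recorded. A positive or negative finding would then be read as covering frequencies that the data may not contain. The Limitations section does not mention bandwidth.
- **Timing.** First-visit data collection is complete for all 120 participants. If the printed rate is right, the band above 11 kHz cannot be recovered for that visit, and only the text and the analysis setting can still change.

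**Working it through.** **Inputs**

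- Sampling rate fs = 22,000 Hz (AE Test With Inmodi Knee Brace).
- Lower filter edge 100 Hz, and literature upper edge 10 to 16 kHz (Signal Segmentation and Denoising). The upper edge is printed irregularly; I read it as a range in thousands of hertz.
- Planned cutoffs 3, 6, 8, 10 and 16 kHz (same section). Only the last is printed in thousands; I read the others the same way.

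**Step 1: highest representable frequency.** fs/2 = 22,000/2 = 11,000 Hz.

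**Step 2: can each cutoff be designed?** The condition is 0 < fc < fs/2. Each was tried as a fourth-order Butterworth bandpass from 100 Hz to fc at fs = 22,000 Hz. The order is my choice and does not affect the condition.

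| Cutoff fc | fc ÷ 11,000 | Filter design |
|---|---|---|
| 3,000 Hz | 0.27 | works |
| 6,000 Hz | 0.55 | works |
| 8,000 Hz | 0.73 | works |
| 10,000 Hz | 0.91 | works |
| 16,000 Hz | 1.45 | rejected: cutoff not below fs/2 |

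**Step 3: does another reading rescue the text?**

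- Taking the list literally as 3, 6, 8 and 10 Hz does not help. Those values fall below the 100 Hz lower edge, and 16,000 Hz still fails.
- Taking 22,000 Hz as a rounding of 22,050 Hz gives fs/2 = 11,025 Hz, still below 16,000 Hz.
- Upsampling would let the filter run, but it cannot restore content that was not recorded.

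**Step 4: what rate would be needed?** A 16 kHz cutoff needs fs > 2 × 16,000 = 32,000 Hz. At exactly 32,000 Hz, fs/2 equals 16,000 Hz and the strict inequality still fails. A rate of 44,100 Hz (fs/2 = 22,050 Hz) would allow it.

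**Step 5: the coverage statement.** Against the literature's upper edges of 10 to 16 kHz:

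- 10 kHz < 11 kHz, so the low end is covered.
- 16 kHz > 11 kHz, so the stretch from 11 to 16 kHz is not. That is 5 kHz, or (16,000 − 11,000)/(16,000 − 100) = 31% of the widest band on a linear frequency scale. This share describes bandwidth only.

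**The case against.** The arithmetic is not open to dispute. The case on the other side concerns how far it reaches, and most of that case stands.

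- **The 20 kHz figure is a ceiling.** A reader might infer that the relevant band fills 0 to 20 kHz, so that (20 − 11)/20 = 45%, nearly half, was never recorded. The article does not support this. It says that relevant information lies below 20 kHz, not that it extends up to there, and it says nothing about how information is spread over frequency. Mel-frequency coefficients, which are among the planned features, also compress the high frequencies. A share of linear hertz is not a share of diagnostic information.
- **Aliasing is not established.** A reader might also infer that energy above 11 kHz has folded back and contaminated the recorded band. That depends on whether it was filtered out before sampling, which the article does not describe. It should not be part of the finding.
- **Either number may be the wrong one.** The filtering section is visibly badly typeset, and the sampling rate could itself be a misprint. It would therefore be premature to say outright that the band is lost.
- **The practical effect is limited.** Four of five settings work. The grid exists to narrow the band, and on data that end at 11 kHz a 16 kHz cutoff would amount to no low-pass filter at all. The ROC-based endpoint, the nested cross-validation and the detectable-correlation calculation are untouched, and the study is declared exploratory.

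What remains is that two printed figures contradict each other and nothing else in the article resolves it. Both are stated outright, so this is not detail left to a fuller protocol.

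**Conclusion.** The point holds as an internal contradiction between the device section and the filtering section. At the stated 22,000 Hz, one of the five planned cutoffs (16 kHz) cannot be implemented. The coverage claim is contradicted for the 11 to 16 kHz part of the literature's upper filter edges, and it holds at the 10 kHz end. It would be too strong to call the claim false for the whole band.

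The conclusion assumes that the printed rate is the true one and that the cutoffs are in thousands of hertz. The second assumption does not matter for the 16,000 Hz setting; the first does, and the article cannot settle it.

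This should be fixed. It limits what the acoustic results can be said to show, without touching the study's other analyses.

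**What to change.** 1. Confirm the true sampling rate, for instance from the stored raw recordings or the device firmware, and reconcile the two sections accordingly.
2. If the rate is 22,000 Hz:
   - delete the 16 kHz setting, so that the grid ends at 10 kHz;
   - replace the coverage sentence with a statement that the recordings represent content below 11 kHz only, which includes the 10 kHz but not the 16 kHz end of the bands used in the cited studies;
   - limit both positive and negative acoustic conclusions to that band;
   - list the unrecorded band above 11 kHz under Limitations.
3. If the rate is a misprint, correct it in the device section. The 16 kHz setting can then stay, provided that the true rate exceeds 32,000 Hz.
4. In either case, print the cutoffs and the literature range with unambiguous units.

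The cost is one check, a few sentences and at most one analysis setting. The downside, if 22,000 Hz is confirmed, is that the claimed acoustic coverage becomes narrower.

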### Feature Extraction

This stage involves the calculation of the outcome parameters that will allow the distinction of different osteoarthritis grades. We will initially rely on state-of-the-art parameters in audio classification, such as spectral analysis (mel-frequency cepstrum coefficients [MFCC]) [36,37] and fractality (the First log-cumulant of the scaling exponent, Global Holder Exponent; paper submitted), average level, peak magnitude (peak amplitude) [38] and click patterns (number of clicks/hits), and number of clicks passing threshold [39].

We will also explore the development of novel features specifically oriented to osteoarthritis classification, such as matched filters of prototype sounds [40].

### Feature Analysis and Multivariate Modeling

In this stage we will study the association between the extracted parameters and osteoarthritis (using the KL or MOAKS grading as the dependent variable), both individually for each feature and also by creating linear and nonlinear multivariate models. For this, we will follow a strategy guided by the principles of (1) increasing complexity and (2) clinical explainability. Thus, the initial models we consider are linear discriminant analysis and logistic regression, which would be ideal options in case we have a reduced number of highly informative and discriminative features. In this ideal scenario, the models would be highly interpretable and easily translatable to a clinical description. In case more sophisticated models are required, we prioritize ensembles of decision trees, such as random forest and gradient boosting, due to the possibility of performing advanced feature importance analysis and derivation of statistical decision rules.

All features will be tested for normality by Shapiro-Wilk tests and presented as mean (SD; normally distributed data) or median and range and, if needed, in histograms, box plots, or violin plots (nonnormal data).

Associations between AE parameters and osteoarthritis (KL or MOAKS grading) will be evaluated using Pearson (normally distributed data) or Spearman (nonnormal data) repeated measures correlation coefficients, as well as with logistic regression models. Mixed ANOVA will be used to compare differences in the AE, osteoarthritis grading parameters between groups. Also, we will specifically assess the relevance of potential confounding variables such as BMI, age, activity level, and gender. The significance level will be set to *P*=.05, and due to the potentially large number of tests, we will apply the Holm post-hoc correction to all *P* values. For multivariate models, the statistical association will be characterized using leave-one-subject-out nested cross-validation, with a subsequent estimation of a confidence interval for prediction accuracy. This is the most conservative and robust cross-validation strategy for overfitting , and with our sample size (n=120), we will have a good estimation of the model variance. Statistical analyses will be done with R (version 4; R Foundation), Matlab (version 2021b or higher; MathWorks, Inc), and Python (version 3.6 or higher; Python Software Foundation).

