**Methods:**

A total of 100 patients with previous reconstructive knee surgery and 20 healthy controls will be examined twice at a 9-month interval for both knees. Acoustic emissions (AE) will be recorded with the Inmodi knee brace (École Polytechnique Fédérale de Lausanne; EPFL) during 4 functional tests (unloaded flexion-extension, sit-to-stand test, one-step test, and walk test). Gold-standard osteoarthritis diagnostics will be assessed and evaluated by an experienced radiologist for (1) the magnetic resonance imaging (MRI) Osteoarthritis Knee Score (MOAKS) and (2) the Kellgren-Lawrence (KL) grading scores. Feature analysis and multivariate modeling will be used to study the association between the extracted sound parameters and osteoarthritis (MOAKS and KL). In addition, thermal images will be taken to investigate the state of inflammation. Participants will fill out 5 health-related questionnaires (Oxford Knee Score [OKS], Core Outcome Measures Index [COMI], University of California at Los Angeles [UCLA ]activity scale, Knee Injury and Osteoarthritis Outcome Score [KOOS], and Forgotten Joint Knee Score-12 [FJS-12]) at both time points.

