## Methods

### Project Design

This is a prospective, single-center, exploratory study. A cross-sectional and a longitudinal dataset will be collected. A total of 120 participants will be recruited and examined twice at a 9-month interval at the Schulthess Klinik in Zurich (see Table 1 for the measurement procedure). The cross-sectional dataset stems from the first visit of the participants and serves for the identification of AE biomarkers for osteoarthritis. The longitudinal dataset combines the data from the first and second visits and tests whether the osteoarthritis changes can be assessed from the biomarkers. A secondary aim is to evaluate the ability of the AE biomarkers from the first visit to predict the condition’s progression as observed during the second visit.

**Table 1. T1:** Summary table with all project visits, including relevant procedures and timelines.

Study period	Information	Screening	1st visit	2nd visit
Time point	Precall (maximum 2 months)	0	0-2 months	9 months (±2 months)
Oral and written information	✓			
Written consent		✓		
Check inclusion/ exclusion criteria		✓		
Anthropometric and patient data			✓	✓
EOS radiography			✓	✓
MRI^a^			✓	✓
Acoustic emission test with Inmodi knee brace			✓	✓
PROMs^b^ (at home)			✓	✓

a MRI: magnetic resonance imaging.

b PROM: patient reported-outcome measurement.

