### Withdrawal and Discontinuation

The patients can withdraw from the study at any point in time. In the declaration of consent, the patient agrees that the data already collected stays in the study. Patients who have knee surgery or a knee injury within the follow-up time or patients who become otherwise severely ill will not be invited for the second visit. In all cases above, the data will be encrypted and used for evaluation. If the enrollment phase is still ongoing, the withdrawn patient will be replaced with a person of the same sex, comparable age, and study group type (A, B1, B2, C1, C2, and D).

If a participant misses the first visit as well as a substitute appointment, the participant will be withdrawn and replaced. If a participant misses the second visit and substitute appointment, his data collected from the first visit will be used.

If a person becomes pregnant, the study will continue but without EOS radiography.

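### Mixed ANOVA is fixed for the group comparisons with no within-person factor named; if visit is that factor, first-visit-only participants, possibly all of Group D, drop out.

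*Protocol article*

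**What the plan says.** The group comparison is specified in one sentence under Feature Analysis and Multivariate Modeling: "Mixed ANOVA will be used to compare differences in the AE, osteoarthritis grading parameters between groups". No within-person factor is named.

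The design offers two candidates. The abstract's Methods paragraph says participants "will be examined twice at a 9-month interval for both knees", and the brace section confirms that the device is used "for AE assessment of both knees simultaneously". Each person can therefore contribute 2 visits x 2 knees = 4 cells. Project Design separates two datasets. Of one it says "The cross-sectional dataset stems from the first visit of the participants and serves for the identification of AE biomarkers for osteoarthritis"; the other is described thus: "The longitudinal dataset combines the data from the first and second visits".

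The Withdrawal and Discontinuation section sets the rules when a return visit does not take place. Non-attendance is covered by this one: "If a participant misses the second visit and substitute appointment, his data collected from the first visit will be used". Another keeps certain patients from returning at all: "Patients who have knee surgery or a knee injury within the follow-up time or patients who become otherwise severely ill will not be invited". Concerning withdrawn and uninvited patients alike, it states that "In all cases above, the data will be encrypted and used for evaluation". The section on missing data covers re-invitation and questionnaire items, but gives no method for an absent second visit.

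Project Population defines six groups of 20; Group D consists of patients already scheduled for unilateral knee replacement. Textbox 1 gives Groups B and C one operated knee and an opposite knee as internal control. It defines no index knee for Group A.

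**The concern.** A classical mixed ANOVA needs every within-person cell filled. If visit is a within-person factor, a participant without a second visit is removed along with the first-visit measurements. The article says those measurements will be used.

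The removal would not be random. The events that bar a second visit (knee surgery, knee injury, severe illness) are plausibly related to the state of the joint. Group D is the most exposed: its members entered the study because knee surgery was booked, and knee surgery during follow-up bars the second visit. The severe end of the osteoarthritis range could thus disappear from the comparison of acoustic and grading parameters.

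If knee is the within-person factor instead, the operated/comparator distinction exists only in Groups B and C. Group D has a knee booked for surgery and a contralateral knee. Group A has two knees with no assigned role.

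**Working it through.** **Inputs from the article.** 120 participants in six groups of 20; two visits; both knees; Group D booked for knee surgery; knee surgery in follow-up bars visit 2.

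**Assumptions.** The article gives neither a second-visit dropout rate nor the timing of surgery in Group D. I take 5-15% loss among the 100 participants in Groups A, B and C, and two extremes for Group D: all return, or none return.

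**The article's own figure.** The smallest detectable correlation is stated as 0.25 for N = 120, 80% power and a 0.05 level. Two-sided Fisher z gives r = tanh((1.960 + 0.842)/sqrt(120 - 3)) = 0.253; the noncentral t gives 0.250. The figure reproduces. It belongs to a proxy correlation model, so below it serves only as a yardstick for the smaller sample.

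**Who stays if visit is a within-person factor.**

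| Group D | Loss in other 100 | Lost | Kept | Smallest detectable r |
|---|---|---|---|---|
| returns | 5% | 5 | 115 | 0.259 |
| returns | 15% | 15 | 105 | 0.270 |
| absent | 5% | 20 + 5 = 25 (20.8%) | 95 | 0.284 |
| absent | 15% | 20 + 15 = 35 (29.2%) | 85 | 0.300 |

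With two knees per person, the first-visit knee records discarded are 2 x 5 = 10 to 2 x 15 = 30 of 240 if Group D returns, and 2 x 25 = 50 to 2 x 35 = 70 if it does not.

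**Precision between the other groups.** If both compared groups lose 5-15%, the standard error is multiplied by 1/sqrt(0.95) = 1.026 to 1/sqrt(0.85) = 1.085, a rise of about 3-8%.

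**Simulated check.** In a dataset of 6 x 20 persons with two visits and two knees, Group D had no second visit and about 10% were lost elsewhere. Of 120 persons, 89 had complete cells, none of them in Group D. A repeated-measures ANOVA routine rejected the full data as unbalanced. A linear mixed model used all 120 persons (418 knee-visit records).

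**If knee is the only within-person factor, at visit 1.** The same routine ran with all 120 persons. For Group A, 2,000 arbitrary assignments of its knees to the two labels gave p values for the knee contrast from 0.0004 to 0.999. Each person's mean over the two knees did not change. Only the knee contrast, and hence the group-by-knee interaction, depends on the label.

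**Form of a replacement model.** A model with separate fixed effects for group, visit, group x visit and a four-level knee status (operated, booked for surgery, comparator, healthy) has 1 + 5 + 1 + 5 + 3 = 15 columns but rank 14, because the healthy level coincides with Group A. The group coefficients against Group A are then not estimable. With one factor for the cells (Group A 1, Groups B1/B2/C1/C2 2 each, Group D 2) there are 1 + 8 + 2 = 11 cells and 11 x 2 = 22 cell-by-visit means, with full rank 22. If Group D has no second visit, the rank is 20: its two visit-2 means are lost, but its visit-1 contrasts with Group A remain estimable.

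**The case against.** The strongest reply is that the article does not say visit is a within-person factor. The sentence speaks of differences between groups, a first-visit dataset is defined, and a first-visit mixed ANOVA with knee as the factor keeps all 120. The promise to use first-visit data does not say in which analysis, and it can be met in the cross-sectional, regression and ROC work. This stands, and it makes the loss conditional. It does not remove the point: the article commits to a method, defines a two-visit dataset, and leaves open a choice that decides who is analysed.

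A reader might infer more than the documents support:

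- *That Group A cannot be represented when knee is a factor.* Both its knees are measured, so the cells are filled. Only the label is undefined, and any model with a knee factor needs the same rule.
- *That 21-29% of participants will be lost.* This needs an empty Group D. The article plans two examinations for everyone and does not give the timing of surgery.
- *That standard errors rise by about 15%.* That is 1/sqrt(0.75), which applies a pooled 25% loss to individual groups. In the scenario above, the remaining groups lose 5-15% each.

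It is also fair to say that the primary endpoint is the area under the ROC curve, and that the group comparison is one supporting analysis in an exploratory study.

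**Conclusion.** The point holds conditionally. With visit as a within-person factor, classical mixed ANOVA discards first-visit data that the article says will be used, and it does so selectively. On the assumed attrition, the cost is 5-15 participants if Group D returns and 25-35 of 120 if it does not. The modest rise in standard error between the other groups matters less than the possible absence of Group D from the comparison. With knee as the only within-person factor at visit 1, nobody is lost, and what remains is an undefined Group A label that leaves a group-by-knee contrast arbitrary. Neither case affects the primary ROC endpoint directly. The correction is cheap and worth making before the group comparisons are run.

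**What to change.** Replace mixed ANOVA by a linear mixed model on all available knee-visit records, with random intercepts for person and for knee within person. Use one fixed factor for the group-by-knee-type cells:

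- Group A: either knee, no index side
- Groups B1, B2, C1 and C2: operated and comparator
- Group D: booked for surgery and contralateral

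Add visit and its interaction with this factor. Do not enter group and a separate healthy-knee status together, since they are aliased. Estimate visit-1 contrasts from all 120 participants, and report change over time only for groups with second-visit data.

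The cost is a few sentences of analysis text; the data and the named software (R, Python) stay the same. There are two downsides. The model relies on missing-at-random, which deserves a stated caveat because the reasons for a missing second visit are related to the knee. And no model can estimate Group D's change over time if that group has no second visit.
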